### 13.5 ANALYSIS DATASETS

The safety analysis set (SAF) includes all participants who receive at least one dose of the OCV-S or Shanchol™. All safety analyses are based on the SAF.

The Full Analysis Set (FAS) is a modified intention to treat (mITT) analysis set includes all participants who receive at least one dose of OCV-S or Shanchol™ and have at least one post-baseline immunogenicity data available.

The per-protocol analysis set (PPS) is comprised of subset of the FAS who receive all their planned vaccine administrations and who have no SMM-assessed important protocol deviations. Analyses on the PPS will be considered for the primary analysis of the immunogenicity endpoints. Participants excluded from the full analysis set for the PPS will be identified and documented prior to locking the study database.

A sensitivity analysis using the FAS will be conducted for the immunogenicity endpoints.

Demographic and baseline characteristics are presented in both PPS and FAS.

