## 4. OBJECTIVES

### 4.1 PRIMARY OBJECTIVES

- To demonstrate non-inferiority of OCV-S compared to Shanchol™ as measured by seroconversion rates of anti-*V. cholerae* O1 Inaba and anti-*V. cholerae* O1 Ogawa vibriocidal titer 2 weeks after second dose for all ages (*i.e.*, one lot of OCV-S)
- To assess and compare safety profile in all age strata combined and describe the safety profile in each age stratum 7 days and 28 days after each dose

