#### 7.2.7.2 DEFINITIVE CONTRAINDICATION

The following conditions/situations listed below, are definitive contraindications and the site investigator must discontinue participants from vaccination:

- 1) Pregnancy, as indicated by a positive urine test.
- 2) An anaphylactic or other significant allergic reaction to the previous dose of vaccine.
- 3) Clinically significant AE or biological abnormality related to previous vaccination and, in the Investigator's opinion, contraindicating further vaccination.
- 4) SAE related to the study vaccine following the previous trial vaccination.

---

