#### 13.1.2 PRIMARY SAFETY ENDPOINT

- Frequency of solicited adverse events within 7 days post vaccination, unsolicited adverse events within 28 days post vaccination, and SAEs after each dose during the entire study period in all ages and in each age stratum.

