#### 13.6.4 PRIMARY SAFETY ENDPOINTS ANALYSIS

The primary safety endpoint analyses are safety analyses of treatment emergent adverse events (TEAEs). TEAEs are defined for this trial as any AEs/ SAEs that occur on or after Day 0 following OCV-S or Shanchol™ administration. All TEAEs will be summarized by frequency, percentage and associated 95% confidence interval. The frequencies will also be presented separately by dose and will be depicted by system order class and preferred term. Additional frequencies will be presented with respect to maximum severity and relationship to investigational product. All serious TEAEs will also be summarized as above. Serious TEAEs will be presented in listings.

---

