**Age Strata: Overall**

| Statistics                       | Total
(N=2529) |     | Group A
(N=330) |   | Group B
(N=331) |    | Group C
(N=934) |    | Group D
(N=934) |    | p-value |
|----------------------------------|-------------------|-----|--------------------|---|--------------------|----|--------------------|----|--------------------|----|---------|
|                                  | n (%)             | m   | n (%)              | m | n (%)              | m  | n (%)              | m  | n (%)              | m  |         |
| Severe                           | 18
(0.71%)     | 23  | 3 (0.91%)          | 4 | 1
(0.30%)       | 1  | 11
(1.18%)      | 15 | 3
(0.32%)       | 3  | 0.0319  |
| Potentially Life-threatening     | 0 (0.00%)         | 0   | 0 (0.00%)          | 0 | 0
(0.00%)       | 0  | 0
(0.00%)       | 0  | 0
(0.00%)       | 0  | NA      |
| Death                            | 0 (0.00%)         | 0   | 0 (0.00%)          | 0 | 0
(0.00%)       | 0  | 0
(0.00%)       | 0  | 0
(0.00%)       | 0  | NA      |
| Relatedness post any vaccination |                   |     |                    |   |                    |    |                    |    |                    |    |         |
| Definitely Related               | 21
(0.83%)     | 28  | 5 (1.52%)          | 7 | 2
(0.60%)       | 5  | 9
(0.96%)       | 11 | 5
(0.54%)       | 5  | 0.2832  |
| Probably Related                 | 46
(1.82%)     | 59  | 7 (2.12%)          | 7 | 4
(1.21%)       | 6  | 20
(2.14%)      | 26 | 15
(1.61%)      | 20 | 0.3936  |
| Possibly Related                 | 76
(3.01%)     | 102 | 7 (2.12%)          | 7 | 7
(2.11%)       | 8  | 26
(2.78%)      | 36 | 36
(3.85%)      | 51 | 0.1965  |
| Unlikely to be Related           | 94
(3.72%)     | 130 | 2 (0.61%)          | 2 | 2
(0.60%)       | 2  | 52
(5.57%)      | 72 | 38
(4.07%)      | 54 | 0.1304  |
| Not Related                      | 60
(2.37%)     | 84  | 6 (1.82%)          | 9 | 9
(2.72%)       | 12 | 24
(2.57%)      | 37 | 21
(2.25%)      | 26 | 0.6508  |

Note: Percentages are based on safety analysis set. The safety analysis set (SAF) includes all participants who receive at least one dose of the OCV-S or Shanchol™.

A Treatment-Emergent AEs are defined as any AEs/SAEs that occur on or after Day 0 following OCV-S or Shanchol™ administration.

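### Post-dose-2 adverse event percentages are divided by everyone who had at least one dose, so they are understated by the share of each group never given dose 2

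*Protocol*

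**What the plan says.** Section 13.5 defines the set: "The safety analysis set (SAF) includes all participants who receive at least one dose of the OCV-S or Shanchol™". It then assigns every safety analysis to it without exception: "All safety analyses are based on the SAF".

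The safety results are nevertheless wanted dose by dose. The second primary objective in 4.1 is, in part, to "describe the safety profile in each age stratum 7 days and 28 days after each dose". The primary safety endpoint in 13.1.2 covers solicited events over 7 days, unsolicited events over 28 days, and "SAEs after each dose during the entire study period in all ages and in each age stratum". Section 13.6.4 asks for frequency, percentage and 95% confidence interval, and adds: "The frequencies will also be presented separately by dose".

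Not everyone in the SAF need receive dose 2. Section 7.2.7.2 lists the definitive reasons for stopping vaccination: pregnancy, a significant allergic reaction, a related SAE, and "Clinically significant AE or biological abnormality related to previous vaccination and, in the Investigator's opinion, contraindicating further vaccination". Section 7.2.9 keeps such participants in the study. No section defines a denominator of participants given dose 2.

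Table S4, appended to the protocol, carries the note "Note: Percentages are based on safety analysis set".

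**The concern.** A participant who never had dose 2 cannot have an event after dose 2. Dividing by the whole SAF counts that participant as someone who took dose 2 and had no event. The percentage then no longer answers the question in the objective, which is how often events follow the second dose in those who take it.

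The error has a fixed sign within each group: the rate after dose 2 can only be understated. It affects a primary safety endpoint, in all ages and in each age stratum. Three of the four definitive stopping reasons in 7.2.7.2 are reactions to the previous dose, so the share missing dose 2 could in principle depend on the vaccine. If it did, the group with more stops would have its post-dose-2 rate lowered further.

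**Working it through.** **Step 1. Reproduce the printed figures.** Inputs are the event counts and group sizes in Table S4 (N = 330, 331, 934 and 934 for Groups A to D, 2529 in total). Rate = participants with an event / SAF N. C is compared with D by an uncorrected Pearson chi-square test.

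| After dose 2 | Group C | Group D | p |
|---|---|---|---|
| Any TEAE | 54/934 = 5.78% | 55/934 = 5.89% | 0.9214 |
| Solicited, 7 days | 15/934 = 1.61% | 31/934 = 3.32% | 0.0169 |
| Unsolicited, 28 days | 46/934 = 4.93% | 36/934 = 3.85% | 0.2587 |

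All agree with Table S4 to the printed digit, as does the total for any TEAE, 123/2529 = 4.86%. The post-dose-2 rows therefore use the at-least-one-dose set.

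**Step 2. Size of the understatement.** If a share d of a group gets no dose 2, then

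printed rate = rate among dose-2 recipients × (1 − d).

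The relative understatement equals d. The protocol does not give d.

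**Step 3. Upper limit on d in Groups A and B.** Section 13.5 requires PPS members to have received all planned vaccinations, so the adult PPS counts in Table S3 are a floor on dose-2 recipients.

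- A: (330 − 308)/330 = 6.7% at most. Any TEAE after dose 2 moves from 8/330 = 2.42% to at most 8/308 = 2.60%.
- B: (331 − 311)/331 = 6.0% at most. It moves from 6/331 = 1.81% to at most 6/311 = 1.93%.

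The true shares should be lower, since the PPS also excludes participants for protocol deviations and Table S3 counts only those with non-missing results.

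**Step 4. Rough proxy for Groups C and D.** Table S2 gives FAS counts by stratum: C 323 + 359 + 243 = 925, D 324 + 355 + 241 = 920. So 9 in C and 14 in D have no post-baseline sample.

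| After dose 2, FAS N | Group C | Group D | p |
|---|---|---|---|
| Any TEAE | 54/925 = 5.84% | 55/920 = 5.98% | 0.90 |
| Solicited, 7 days | 15/925 = 1.62% | 31/920 = 3.37% | 0.016 |
| Unsolicited, 28 days | 46/925 = 4.97% | 36/920 = 3.91% | 0.27 |

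The largest shift is 0.09 percentage point (any TEAE, Group D). This is only a proxy: the Day 14 sample is drawn before dose 2, so a FAS member may still have missed dose 2.

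**Step 5. What would disturb the comparison.** Equal d in both groups leaves it almost unchanged. At an assumed 5% in each, solicited events are 1.69% against 3.49%, p = 0.0168. The order of C and D for any TEAE reverses only if C has about 17 fewer dose-2 recipients than D: 934 × 54/55 = 917.0, and 934 − 917 = 17.

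**The case against.** **The denominator may be left open.** One can argue that 13.5 names a population, that SAF members who took dose 2 are still drawn from it, and that table denominators belong in a statistical analysis plan that is not shown. This does not stand. Section 13.5 puts all safety analyses on one set and 13.6.4 asks for percentages by dose. Table S4 shows that rule carried out.

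**A between-vaccine bias is not shown.** This stands. A reader might infer that the vaccine causing more stops is being made to look safer. That needs unequal non-receipt, and the documents report no stops by group. The proxy shows less loss in C than in D (9 against 14). Participants with a severe event after dose 1 numbered 6 in C and 1 in D. Had all of them been stopped, any TEAE after dose 2 would be 54/928 = 5.82% against 55/933 = 5.89%, with no reversal. Even a reversal would swap two rates that differ with p = 0.92.

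**The sample-size dropout is not a rate of missing dose 2.** This also stands. A reader might apply the 10% from 13.2, which would put any TEAE in D at 55/841 = 6.54%. That figure is an allowance in the immunogenicity calculations, and nothing places all of it before dose 2.

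**A fall from dose 1 to dose 2 is not generally exaggerated.** A reader might infer this too, but there is often no fall. In D, any TEAE rises from 4.93% to 5.89% and solicited events from 2.78% to 3.32%. Unsolicited events rise in both C and D.

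**A dose-2 denominator has its own selection.** It keeps those who tolerated dose 1, whereas the SAF stays close to the groups as randomised. This is correct and shapes the remedy. Section 13.6.6 gives reasons for study discontinuation by group, but that does not clearly cover participants who stop vaccination and remain in follow-up.

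**Conclusion.** The point holds as a wrong denominator with a known sign and a size that is probably small. Every post-dose-2 percentage is understated, in relative terms, by the share of that group not given dose 2. For adults in Groups A and B that share is at most 6.7% and 6.0%. In Groups C and D the proxy suggests shifts of about 0.1 percentage point or less, with no changed conclusion.

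The limits for A and B assume that Tables S3 and S4 assign participants to groups in the same way. The figures for C and D rest on FAS counts standing in for dose-2 recipients. A difference in bias between OCV-S and Shanchol remains a possibility under 7.2.7.2, not a finding. Section 13.3 makes the safety comparison descriptive, so no formal safety test turns on this, and the any-vaccination summaries are unaffected. It still merits correction, because the by-dose profile is a primary safety endpoint and the reader cannot recover the right rate from what is reported.

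**What to change.** In 13.5 and 13.6.4:

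- Keep the SAF as the denominator for post-dose-1 and any-dose summaries.
- Use SAF participants who received dose 2 as the denominator for all post-dose-2 summaries, overall and by age stratum, with that N in the column header.
- Beside those summaries, give the number not given dose 2 and the reasons, by group. This is needed because the dose-2 denominator still selects those who tolerated dose 1.

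The cost is a sentence or two of text, a second denominator in the safety tables, and slightly higher post-dose-2 rates.

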### 13.6 DESCRIPTION OF STATISTICAL METHODS

#### 13.6.1 GENERAL APPROACH

This is a randomized, observer-blinded phase III study in healthy participants aged 1 to 40 years old at the time of vaccination of investigational vaccine to assess immune non-inferiority and safety of OCV-S (Group C) compared to Shanchol™ (Group D) and lot consistency among three lots of OCV-S (Group A, B, and C) in adults.

Unless otherwise specified, standard descriptive statistics will be computed for all endpoints and other observed values. The standard descriptive statistics for continuous variables include number of observations analyzed, mean, standard deviation, median, minimum, and maximum. The standard descriptive statistics for categorical variables include frequency distribution with the

number and percent of participants included in each category. The binary outcome measures of safety and immunogenicity will be summarized with frequency, proportion and associated 95% confidence interval. The continuous outcome measures of immunogenicity will be summarized with geometric mean and associated 95% confidence interval. The outcome measures will be summarized by study group and for overall ages and by age strata.

Statistical significance will be compared using two-sample t-test or ANOVA test for continuous variables, and Chi-square test or Fisher's exact test for categorical variables.

Missing immunogenicity data will not be imputed for the analysis. If missing data is more than 10%, the analysis of missing pattern will be assessed, and a multiple imputation technique will be utilized as a sensitivity analysis.

---

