## 7. STUDY DESIGN AND CLINICAL PROCEDURES

### 7.1 DESCRIPTION OF THE OVERALL TRIAL DESIGN AND PLAN

#### 7.1.1 TRIAL DESIGN

This is a multicenter, randomized, observer-blinded, controlled study to evaluate immune non-inferiority and safety of OCV-S compared to Shanchol™ in 1 to 40 years old healthy Nepalese participants. Lot-to-lot consistency will be included as a secondary objective. The vaccines will be administered to 2,530 healthy participants. 1,595 participants will be vaccinated with an investigational vaccine (OCV-S) and 935 healthy participants will receive an active control vaccine (licensed Shanchol™). Each participant will be vaccinated with either OCV-S or Shanchol™ twice by 2 weeks apart. Participants will be followed up for 2 weeks after each dose for immunogenicity (blood samples at Day 0, Day 14 prior to first and second vaccination respectively, and Day 28) and for 24 weeks after the second dose for safety assessment. The primary objective is to demonstrate non-inferiority of OCV-S to Shanchol™ as measured by seroconversion rates of vibriocidal titers against *V. cholerae* O1 Inaba and *V. cholerae* O1 Ogawa 2 weeks after second dose for all ages. The secondary objectives are to demonstrate non-inferiority of OCV-S compared to Shanchol™ as measured by GMT and seroconversion rates of vibriocidal titers against *V. cholerae* O1 Inaba and *V. cholerae* O1 Ogawa 2 weeks after second dose for all ages and in each age stratum. The equivalence of immunogenicity will be demonstrated as measured by GMT and seroconversion rates of vibriocidal titers against *V. cholerae* O1 Inaba and *V. cholerae* O1 Ogawa of 3 lots of OCV-S 2 weeks after second dose in adults. Safety profile will be assessed and compared in all age strata combined and described in each age stratum 7 days and 28 days after each dose. Exploratory objective will describe vibriocidal antibody responses 2 weeks after first dose for all ages and for each age stratum. The study has been designed to consider only one lot in the analysis of the primary immunogenicity endpoint in order to reduce the chance that a single consistency lot not meeting the criteria could result in the study not meeting the primary immunogenicity endpoint. To reduce the risk of failing the lot-to-lot consistency objective, it was designed to conduct the lot-to-lot consistency in only adults where immune responses to vaccine may have less inherent variability.

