## 13.3 STATISTICAL ANALYSIS PLAN

The statistical analysis will focus on comparisons of immunogenicity of OCV-S (Group C) and Shanchol™ (Group D), and on tests of lot consistency of OCV-S (pair-wise comparison of Group A, B and C in adults) at 2 weeks post second dose of vaccination. Safety of OCV-S will be assessed by descriptively comparing incidence of common solicited, unsolicited and serious AE between OCV-S and Shanchol™ and any incidence of unexpected AE. The statistical analysis will be performed when all participants complete the Day 182 visit (24 weeks post second dose). Immunogenicity and safety data up to Day 182 will be included in the analysis.

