Group A, B and C are three different lots of OCV-S and Group D is Shanchol™, respectively.

"p-value" is the comparison between the number of subjects in Group C and Group D.

Chi-square test is used to calculate "p-value". Fisher's test is used if more than 20% of expected cell frequency is <5.

Abbreviations: n = Number of Subjects with Adverse Events; m = Number of Adverse Events; AE = Adverse Events; TEAE = Treatment Emergent Adverse Events; SAE = Serious Adverse Events.

[figure not shown]

**Figure S1. 95% Confidence Intervals (CI) of adjusted Geometric Mean Ratio (GMR) (Euvichol-S/ Shanchol™) for *V.cholerae* O1 Ogawa (A) and Inaba (B)**

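### The primary safety comparison has no confidence interval for the between-vaccine difference; the only between-group statistic that reaches it is a general chi-square/Fisher sentence

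*Protocol*

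**What the plan says.** Protocol 4.1 makes safety the second primary objective: "To assess and compare safety profile in all age strata combined and describe the safety profile in each age stratum 7 days and 28 days" (both periods counted from each vaccination). Section 13.3 describes the method in words: "Safety of OCV-S will be assessed by descriptively comparing incidence of common solicited, unsolicited and serious AE between OCV-S and Shanchol™". It names no effect measure.

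Two sections give intervals for safety data. Section 13.6.1 states: "The binary outcome measures of safety and immunogenicity will be summarized with frequency, proportion and associated 95% confidence interval". Section 13.6.4 states: "All TEAEs will be summarized by frequency, percentage and associated 95% confidence interval". Section 13.6.1 adds that outcome measures are summarised by study group and age stratum, so these are intervals for single proportions.

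The one sentence that compares groups on categorical data in general is in 13.6.1: "Statistical significance will be compared using two-sample t-test or ANOVA test for continuous variables, and Chi-square test or Fisher's exact test for categorical variables". It names no endpoint, significance level or sidedness, and it is not confined to baseline variables. Section 13.4 lists hypotheses for immunogenicity only.

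Table S4, among the results tables at the end of the protocol document, compares Group C with Group D on adverse-event counts. Its footnote reads: "Chi-square test is used to calculate 'p-value'. Fisher's test is used if more than 20% of expected cell frequency is <5". It has no column for the difference or its interval.

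**The concern.** A comparison of two vaccines on safety needs an estimate of the difference and a statement of how large an excess the data still allow. A significance test of no difference supplies neither. A p-value above 0.05 can go with a narrow interval around zero or with a wide one that includes a relevant excess, and the reader cannot tell which.

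The gap stands out because the protocol handles immunogenicity differently. Sections 13.6.3, 13.6.5 and 13.6.10 give a 95% interval for the difference in seroconversion or the ratio of GMTs, even for exploratory comparisons. A primary objective therefore gets less than an exploratory one.

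At stake is how the safety result is reported and read. The data to give the interval are already collected.

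**Working it through.** **1. What each section gives for a between-vaccine comparison**

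| Outcome | Section | Between-group quantity |
|---|---|---|
| Seroconversion, all ages | 13.6.3 | Difference with 95% CI |
| GMT; seroconversion by stratum; lots | 13.6.5 | Ratio or difference with 95% CI |
| Exploratory immunogenicity | 13.6.10 | Difference or ratio with 95% CI |
| Safety | 13.3 | Descriptive comparison, no statistic named |
| Safety | 13.6.4 | 95% CI for rates only |
| Categorical variables in general | 13.6.1 | Chi-square or Fisher test |

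The protocol states no power or detectable event rate for safety, so there is no safety figure to reproduce.

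**2. What an interval adds to Table S4**

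The inputs are the Table S4 counts, 934 per group. The interval is the unstratified Miettinen-Nurminen score interval, because stratum counts are not in the table.

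- Unsolicited events after any dose: 75/934 = 8.03% versus 58/934 = 6.21%. The difference is (75 - 58)/934 = +1.8 points. Chi-square p = 0.126, which matches the table's 0.1261. The 95% CI is **-0.5 to +4.2 points**, so an excess of about 4 per 100 is not excluded.
- Severe events after any dose: 11/934 = 1.18% versus 3/934 = 0.32%. The difference is (11 - 3)/934 = +0.9 points. Chi-square p = 0.032, which matches the table's 0.0319; Fisher's exact test gives 0.056. The 95% CI is **+0.1 to +1.8 points**. The two tests named in 13.6.1 fall on opposite sides of 0.05. The interval gives the size of the excess, which neither p-value does.

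**3. How often the test misses a real increase**

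The inputs are 935 per arm (Groups C and D, Table 1) and two rates that Protocol 3.3.1 reports for Euvichol/Euvichol-Plus: 1.17% (gastrointestinal reactions over 28 days) and 3.40% (solicited reactions over 7 days). Two-sided 0.05 is an assumption, because the protocol sets no level for safety.

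Power = Φ[(p1 - p2 - 1.96·s0)/s1], where s0 = √(2·p̄(1 - p̄)/n), p̄ is the mean of the two rates, and s1 = √((p1(1 - p1) + p2(1 - p2))/n).

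- 1.17% to 2.34%: s0 = 0.006073 and s1 = 0.006067. Power = Φ[(0.0117 - 0.01190)/0.006067] = Φ(-0.03) = 0.49, so **51% missed**.
- 3.40% to 6.80%: s0 = 0.010175 and s1 = 0.010144. Power = Φ[(0.0340 - 0.01994)/0.010144] = Φ(1.39) = 0.92, so **8% missed**.

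Simulation with the Table S4 test rule (10,000 trials, counting only an excess on OCV-S) gave 50% and 8%. With all OCV-S recipients against Shanchol (1,595 versus 935), the same doublings are missed 45% and 4% of the time.

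**4. Precision of the interval**

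With a true rate of 1.17% in both arms, the half-width is 1.96·√(2 × 0.0117 × 0.9883/935) = 0.0097, about 1.0 percentage point.

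**The case against.** The strongest reply is that the protocol does not rest safety on a test. Section 13.3 calls the comparison descriptive, and 13.4 gives safety no null hypothesis, margin or success criterion. The sections written for safety name no test, and the 13.6.1 sentence is a general one. This stands, and it rules out a stronger reading. A reader might infer that similar safety will be concluded from p > 0.05, or that safety is a tested co-primary hypothesis. The protocol states neither. Reading non-significance as similarity is a foreseeable misreading of a table of p-values, not a rule of the plan.

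A second reply is that the miss rates reflect rare events and sample size, and that an interval from the same data has no more power. This is also right: the interval shows the imprecision but does not remove it. For common events the test is adequate, as the 3.40% case shows. Table S4 also has rows where the test flagged a difference, in both directions: severe events after any dose (11 versus 3, p = 0.0319) and solicited events after the second dose (15 versus 31, p = 0.0169).

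A third reply is that the interval method and table columns belong in the statistical analysis plan, which is not shown. That would answer a complaint about mere absence. But the protocol itself sets effect intervals for the immunogenicity comparisons, leaves safety with a general test sentence, and calls the same comparison descriptive elsewhere. Table S4 shows that the test was applied to adverse events without an interval.

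**Conclusion.** The point holds as a matter of estimation and reporting. The protocol calls the primary safety comparison descriptive, yet the only between-group statistic that reaches it is a test of no difference, and no interval for the difference is specified. Table S4 follows this pattern.

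The consequence is moderate and depends on the event rate. For unsolicited events, p = 0.13 leaves an excess of up to 4.2 points not excluded. A doubling is missed about half the time at 1.17% but only about 8% of the time at 3.40%. These miss rates assume a two-sided 0.05 test, 935 per arm and the earlier vaccines' reaction rates. The Table S4 intervals are unstratified. None of this shows that OCV-S is less safe or that the trial drew a wrong safety conclusion.

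**What to change.** In 13.6.4, make the between-vaccine safety comparison the Group C minus Group D risk difference with a two-sided 95% score (Miettinen-Nurminen) interval, stratified by the three randomised age strata. Report it for any solicited event within 7 days, any unsolicited event within 28 days, severe events and SAEs. Groups C and D are the like-for-like pair, because Groups A and B enrol adults only.

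In 13.6.1, state that chi-square and Fisher p-values for safety outcomes are descriptive only, which brings the sentence into line with 13.3.

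The cost is wording and a few table columns, with no new data or participants. The downside is that intervals for rare events will be visibly wide.
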